### Sample size calculation

To determine the impact of online PA management support on eGFRcys, we will examine between-group differences in eGFRcys. Since there have been no reports of a clinically meaningful minimum difference in eGFRcys among patients with ACS, we arbitrarily assumed that the between-group difference in eGFRcys after 3 months would be five mL/min/1.73 m^2^. If the standard deviation of eGFRcys in both groups is set to be 16.0 in reference to our previous study (Sato et al., 2019), the effect size was 0.3125.

Subsequently, assuming that between-group comparisons of eGFRcys after 3 months would be performed using ANCOVA with baseline values as covariates, G*Power 3.1 was used to calculate the required sample size with an effect size *f* = 0.3125, alpha = 0.05, and power = 0.8. The results showed that 83 cases were detected. Accordingly, we calculated that the required sample size was 83 cases, and the target number of cases was set at 88 (44 in the intervention group and 44 in the control group), taking into account the possibility of dropouts (5%) in both groups.

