### Statistical analysis

In this study, the analysis will involve an intention to treat analysis. Therefore, patients’ consent will be obtained to use 3-month post-assessment information derived from the observed clinical data in the event of dropout or poor adherence in the intervention arm. Regarding background information of participants, discrete data, including frequencies, proportions, and 95% confidence intervals, will be calculated for each group. For continuous data, the mean, standard deviation, and 95% confidence interval will be calculated for each group.

The primary outcome, eGFRcys, will be examined using analysis of covariance (ANCOVA), with adjustment for baseline values as covariates for the least squares mean of eGFRcys at 3 months. Secondarily, between-group comparisons of the change in eGFRcys will be performed in the same way.

The secondary endpoints of ACR, BNP, average number of steps, peak VO2, and EQ-5D will be analyzed using ANCOVA, with adjustment for baseline values. Between-group comparisons of the incidence of adverse events will be performed using the *χ*-square test.

All statistical analyses will be performed using SPSS version 29.0 (IBM Corp., Armonk, NY, USA). Statistical significance will be set at an alpha-level of 0.05.

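### The sample size calculation enters Cohen's d (5/16 = 0.3125) into G*Power as Cohen's f, so 80% power with 83 patients does not follow from the stated difference and SD

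*Protocol article*

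**What the plan says.** All the inputs stand under Sample size calculation in the protocol article.

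- Difference: "we arbitrarily assumed that the between-group difference in eGFRcys after 3 months would be five mL/min/1.73 m^2".
- Variability: "If the standard deviation of eGFRcys in both groups is set to be 16.0", with an earlier study by the same team as the source.
- From these two figures, "the effect size was 0.3125".
- Test: "assuming that between-group comparisons of eGFRcys after 3 months would be performed using ANCOVA with baseline values as covariates".
- Software step (G*Power 3.1): "calculate the required sample size with an effect size *f* = 0.3125, alpha = 0.05, and power = 0.8".
- Result: 83 patients, raised to a target of 88 (44 per arm) for an assumed 5% dropout.

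The Statistical analysis section names the same baseline-adjusted ANCOVA for the primary outcome and adds "Statistical significance will be set at an alpha-level of 0.05". The article gives no baseline to 3-month correlation, no R² and no residual SD. It does not say that 16.0 is an adjusted SD or an SD of change.

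**The concern.** The same number, 0.3125, appears first as a mean difference divided by an SD and then as f. These are different quantities. Cohen's d is the distance between two means in SD units. Cohen's f is the SD of the group means around their grand mean, in within-group SD units. With two equal groups each mean lies half the difference from the centre, so f = d/2. Using d in place of f doubles the assumed effect and cuts the required sample size to about a quarter.

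This is the only justification given for the size of the trial, and it concerns the primary endpoint. If the stated power is wrong, a reader of a non-significant result has no sound basis for judging whether a 5-unit effect has been made unlikely or simply could not be seen.

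**Working it through.** **Inputs** (Sample size calculation): difference 5; SD 16.0; α = 0.05; target power 0.80; two equal groups; ANCOVA with one covariate; 5% dropout.

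**Formula.** G*Power's ANCOVA F test for two groups and one covariate uses a noncentral F distribution with df1 = 1, df2 = N − 3 and noncentrality λ = f²N.

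**Step 1: reproduce the stated figure.** With f = 0.3125:
- N = 82 gives power 0.798.
- N = 83 gives power 0.803, with λ = 0.3125² × 83 = 8.11.

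So 83 is the smallest N that reaches 80%, an exact match. The dropout step also matches: 83/0.95 = 87.4, rounded up to 88.

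**Step 2: the f that the stated inputs imply.** The group means lie 2.5 on either side of the grand mean, so f = 2.5/16 = 0.15625 = d/2. Read backwards, f = 0.3125 means a difference of 2 × 0.3125 × 16 = 10 at SD 16, or an SD of 5/(2 × 0.3125) = 8 at a difference of 5.

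**Step 3: power on the stated difference and SD, with no credit for baseline.** With f = 0.15625:
- N = 83: λ = 0.15625² × 83 = 2.03, power 0.290.
- N = 88: power 0.305.
- 80% power needs N = 324 (342 after 5% dropout, since 324/0.95 = 341.1, rounded up).

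A normal-approximation check for two means gives 0.296 at 83 patients and 161 per arm (322 in total) for 80% power, in agreement.

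**Step 4: credit for baseline adjustment, if 16.0 is the SD of raw values.** The ANCOVA residual SD is 16 × √(1 − r²), so f = 0.15625/√(1 − r²). The document does not give r, so the table shows a range. The last column is the difference detectable with 80% power at N = 83, which is 10 × √(1 − r²).

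| r | f | Power, N = 83 | Power, N = 88 | N for 80% | Detectable difference |
|---|---|---|---|---|---|
| 0 | 0.156 | 29% | 31% | 324 | 10.0 |
| 0.5 | 0.180 | 37% | 39% | 244 | 8.7 |
| 0.7 | 0.219 | 50% | 53% | 166 | 7.1 |
| 0.8 | 0.260 | 65% | 68% | 118 | 6.0 |
| 0.85 | 0.297 | 76% | 79% | 92 | 5.3 |
| 0.9 | 0.359 | 90% | 91% | 64 | 4.4 |

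Power at N = 83 reaches 80% at r of about 0.865. An f of exactly 0.3125 requires √(1 − r²) = 0.5, that is r = √0.75 = 0.866.

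**Step 5: other meanings of 16.0.**
- Residual SD: f stays at 0.15625 and power at N = 83 stays at 29%.
- SD of change, with equal variances at the two times: the ANCOVA residual SD is 16 × √((1 + r)/2). At r = 0.5 this is 13.86, f = 2.5/13.86 = 0.180 and power is 37%. At r = 0.7 it is 14.75, f = 0.169 and power is 33%.

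**The case against.** The strongest reply is that 29% is not the power of the planned analysis. The protocol fixes an ANCOVA adjusted for baseline eGFRcys, and 16.0 reads most naturally as the SD of raw values. On that reading 29% would require a patient's eGFRcys at discharge to carry no information about the value three months later. With r above roughly 0.87, 83 patients are enough for 5 units, and nothing in the document rules that out.

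This stands as a limit on the size of the problem. A reader might infer that the trial has about 29% power, or that it has been shown to be underpowered. The document supports neither: 29% is a floor, and the actual power for 5 units is undetermined without r. It does not rescue the calculation, however. The effect size is formed as 5/16 with no adjustment, no correlation is invoked, and 83 reproduces with no further input. A high r could bring the real power to 80% only by coincidence.

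Two other replies are weaker. The target difference is openly called arbitrary, so no established clinical threshold is misrepresented; but the 80% power claimed for it still does not follow. A one-sided test is not stated, the ANCOVA F test has no direction, and a one-sided 0.05 test would give only about 41% at 83 patients without credit for baseline.

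**Conclusion.** The point holds as a wrong statement in the sample size paragraph: d was used as f, and 80% power for a 5 mL/min/1.73 m² difference at SD 16.0 with 83 patients does not follow from the inputs given. The exact match at N = 83 leaves little doubt about how it happened.

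How far actual power falls short, if it does, depends on two facts the article does not give: what kind of SD 16.0 is, and the correlation r. Across the readings and values of r shown above, power at 83 patients runs from 29% to 90%, and 80% is reached only if 16.0 is a raw SD and r is at least about 0.865. The primary analysis and its type I error are unaffected.

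**What to change.** Rewrite the sample size paragraph.

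1. Compute f as half the standardised difference (0.15625 before any adjustment).
2. State whether 16.0 is the SD of raw values, of change or of residuals.
3. Give r with its source; the team's own earlier cohort is the obvious place to look. If 16.0 is a raw SD, use f = 0.15625/√(1 − r²). If it is an SD of change or of residuals, use the matching form in Step 5.
4. Restate either the power for 5 mL/min/1.73 m² or the difference detectable with 80% power at 83 evaluable patients. If 16.0 is a raw SD, that difference is 7.1 at r = 0.7, 6.0 at r = 0.8 and 4.4 at r = 0.9; with no credit for r it is 10.0.

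The cost is one corrected paragraph and, probably, a less favourable stated power. Correcting the statement does not require more patients. Whether to enlarge the trial is a separate decision for the sponsor, to be made once r is known.

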## Discussion

This randomized controlled trial will provide evidence regarding the effectiveness of online support for PA management in renal protection after ACS. In patients with ACS, combined renal dysfunction has been associated with increased overall mortality and cardiovascular events.

Previous studies have shown that PA management (Sato et al., 2019; Sato & Kohzuki, 2021; Sato et al., 2021; Sato et al., 2024) and outpatient CR (Takaya et al., 2014) may reduce renal function decline in patients after ACS. However, this evidence remains uncertain since it has been exclusively obtained from observational studies. Furthermore, the low CR participation rate of patients with ACS in practice has impeded the feasibility of PA management as a renal protection strategy.

The ultimate goal of this study is to develop a more feasible renal protection strategy that addresses these challenges. Therefore, we focused on wearable device and web application technologies to design an online support intervention of PA management suitable for renal protection in patients with ACS. The strength of this intervention is its ability to monitor daily PA, pulse, blood pressure, and other biometric information in real time as well as to provide educational feedback and goal setting based on this information. This allows patients with ACS to engage in PA improvement with remote support from a physical therapist or physician without having to visit the hospital, and may be an alternative to the late phase II CR. This novel strategy not only removes barriers impeding outpatient CR participation and protects cardiac and renal function in patients with ACS, but also may improve survival and recurrence rates, avoid dialysis, and reduce medical and long-term care costs.

In addition, the primary endpoint in this study is the eGFRcys, which is less sensitive to skeletal muscle mass and diet. This will minimize the possibility that changes in skeletal muscle mass will mask the relationship between increased PA and changes in renal function, and therefore enhance the scientific nature of our findings.

##  Supplemental Information

10.7717/peerj.19067/supp-1Supplemental Information 1CONSORT checklist
